## Abstract

**Background:**

To assure patient-centred end-of-life care, palliative interventions need to account for patients’ preferences. Advance care planning (ACP) is a structured approach that allows patients, relatives and physicians to discuss end-of-life decisions. Although ACP can improve several patient related outcomes, the implementation of ACP remains difficult. The col-ACP-study (collaborative advance care planning) will investigate a new ACP procedure (col-ACP-intervention (German: Hand-in-Hand Intervention)) in palliative cancer patients and their relatives that addresses individual values and targets barriers of communication before an ACP process.

**Methods:**

In a randomised controlled trial, 270 cancer patients without curative treatment options and their relatives will receive either 1) col-ACP 2) a supportive intervention (active control group) or 3) standard medical care (TAU). col-ACP comprises two steps: a) addressing various barriers of patients and relatives that discourage them from discussing end-of-life issues followed by b) a regular, structured ACP procedure. The col-ACP-intervention consists of 6 sessions. Primary endpoint is the patients’ quality of life 16 weeks after randomisation. Secondary endpoints include measurements of distress; depression; communication barriers; caregivers’ quality of life; existence of ACP or advance directives; the consistence of end of life care; and others. Patients will be followed up for 13 months. Multivariate analyses will be carried out. Qualitative evaluation of the intervention will be conducted.

**Discussion:**

Augmentation of a regular ACP program by a structured psycho-oncological intervention is an innovative approach to target barriers of communication about end-of-life issues. Study findings will help to understand the value of such a combined intervention in palliative care.

**Trial registration:**

ClinicalTrials.gov Identifier: NCT03387436 (Date of registration: 01/02/2018, retrospectively registered.

## Background

Cancer is one of the major causes of death in developed countries. According to the Global Cancer Observatory there were 18.1 million new diagnoses and 9.6 million cancer related death in 2018 [1]. A high quality of end-of-life care, according to individual patient’s wishes and values has become an important goal of palliative care [2–4]. To achieve these goals, patient’s preferences for end-of-life (EoL) care need to be known [5]. However, a considerable part of these patients cannot express wishes or values in their end-of-life period due to disease based cognitive impairment [6]. Therefore, communication about end-of-life care needs to be in time. Additionally, optimal communication between patients, their family and their physicians has been identified to be one of the most important aspects of medical care at the end of life [7, 8]. In fact, end-of-life discussions occur usually infrequent, too late and are often crisis-orientated and restricted to decisions about life-sustaining treatments, which can cause relevant distress in patients and relatives [6, 9]. Also, unmet needs during EoL care are commonly reported by bereaved family members [10]. Although advance directives were designed to diminish these problematic issues, they are less common than expected [11–13]. Additionally, traditional advance directives have shown several points of weakness in daily clinical routine [14].

To overcome these challenges, a great effort has been made since the 1990s establishing the idea of advance care planning (ACP). An international consensus supported by the European Association for Palliative care defines it as follows: “Advance care planning enables individuals to define goals and preferences for future medical treatment and care, to discuss these goals and preferences with family and health-care providers, and to record and review these preferences if appropriate” [15]. There is evidence that ACP-interventions can improve patient-related outcomes such as patient satisfaction with care, consistency of actual care and patients´ goals, quality of communication and shared decision-making [16].

However, implementation of ACP is facing many organisational and individual psychological barriers. The first include: lack of integration into workflow as well as lack of information and involvement of involvement of clinical carers in the ACP process and its documented outcomes. Additionally, system-wide implementation of complex ACP interventions remains difficult as a review of Lund et al. demonstrates [17]. Even if organisational barriers are low, ACP is not inquired as frequently as expected because of cultural and psychological barriers that hinder a frequent realization of ACP and communications about EoL wishes. Those barriers include fear of own death and of burdening relatives, unawareness of gravity of disease, “optimism”, aversive emotional responses to reflecting death and avoidance of end-of-life topics [7, 8, 18, 19].

A complex intervention might improve implementation of ACP and enable EoL care that is concordant with patient wishes. This complex ACP intervention should address barriers of engagement and can thus enhance EoL communication, ACP implementation and improve quality of life and EoL care in cancer patients with limited disease prognosis. A recent systematic review stated that multi-focal interventions may effectively remove barriers to end-of-life communication [16]. Such multi-focal interventions may include amongst others a) facilitation of communication by specifically trained personnel, b) advance care planning, c) structured communication roles, responsibilities and processes, d) summarising patient end-of-life preferences and values using a questionnaire with feedback of this summary document to clinicians and e) psychoeducation for patients and relatives [16, 19, 20].

Acknowledging these findings, the present randomised controlled trial investigates the effectiveness and efficacy of an innovative, collaborative ACP intervention regarding the quality of life of patients and relatives. The intervention targets psychosocial barriers of patients and relatives towards EoL discussions prior to a standardised ACP process (“beizeiten begleiten” [21] German adaptation of “respecting choices”). We hypothesise that combining psycho-oncological tools with standardised ACP can be an innovative approach to improve EoL care and quality of life of cancer patients, as this is a central goal of palliative care [22]. Because of its multi-professional aim the intervention is called **col**laborative **a**dvance **c**are **p**lanning (col-ACP).

The main research questions are:
Can col-ACP improve quality of life in palliative patients and relatives?Does col-ACP influence distress, anxiety and communication barriers in patients and relatives and enhance consistent end-of-life care?Does col-ACP influence patient relative communication about EoL topics?

## Methods/design

### Study design and setting

The col-ACP-study is a randomised controlled trial designed to evaluate the efficacy and effectiveness of a collaborative advance care planning intervention. Three intervention arms will be compared longitudinally. We will screen and recruit palliative cancer patients from multiple settings of the German health care system. Our screenings sites are:
University hospital of the Philipps-University Marburg – department of haematology/oncology, department of oncological urology, department of oncological gastroenterology, department of radiation therapy; patients are recruited from inpatient and outpatient settingsClinic for oncological rehabilitation “Sonnenblick”, MarburgSpecialised ambulant palliative care team of the county Marburg-Biedenkopf

The respective sites were chosen, since – taken together - they cover approximately 90% of all specialised palliative care services for patients in our district (Marburg-Biedenkopf). Integrating all these sites in our recruitment strategy increases the representativeness of our approach.

### Study population

The study will recruit 270 adult cancer patients with non-curable disease. The trial is open to all neoplastic entities. Patients are screened with the `surprise question‘. Cancer patients with these characteristics have a high likelihood of dying in the next year [23]. However, patients are excluded if the treating physician is certain that the patient will not survive at least 4 months after randomisation. Exclusion criteria are the inability to perform the study intervention (e.g. ECOG ≥ 3), insufficient German language skills and cognitive inability to give informed consent.

### Study procedures

Medical treatment of patients is independent from the study procedures and will be carried out accordingly to the respective cancer guidelines. The study intervention is an addition to the medical treatment as usual.

Patients are screened for eligibility by their treating physician; this process is taking place individually at each screening site. Patients who meet inclusion criteria are approached by a licensed physician. They are informed in writing and verbally about the study and invited to partake with a relative or close friend. After written consent and collection of baseline assessment, patients are admitted to the study and randomised equally to one of three study arms (Fig. 1). Participation is voluntary and can be withdrawn at any time. All collected data can be requested and deleted by patients according to EU data privacy policy. Patients will be randomised in the following arms: Treatment as usual (TAU), active control group (ACG), study intervention (col-ACP). If patients decline to participate, they can contribute to the non-randomised control-group.

**Fig. 1 Fig1:**
[figure not shown]
Study Design

### Power calculation, sample size, recruitment

Sample size of 77 per group were calculated with a two-sided significance level of α = 5% to achieve a power of 80% to reject at least one comparison, when at least one difference between groups has an effect size of d = 0.5. This effect size was determined assuming a minimal important difference of 5 (71) and a standard deviation of approximately 10 (72). Assuming a drop-out rate (meaning no QoL (Quality of life) data available after intervention, see 7) of 20%, 90 patients per group should be recruited. We have to expect about 130 to 155 events of death in our patient population depending on the assumption of the one-year survival rate. The primary hypotheses will be analyzed using a linear mixed model, which will provide estimates for missing values. Compared to intention-to-treat analyses with last-observation-carried forward methods, this procedure provides better estimates for missing data using the full data sample (intention-to-treat sample), and addresses individual differences more adequately.

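### The sample size figures do not fit together: 77 evaluable per group at 20% drop-out needs 97 recruited, and the planned 90 leaves 72

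*Protocol article*

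**What the plan says.** All the figures stand in the protocol article under Power calculation, sample size, recruitment. The base number is given as "Sample size of 77 per group were calculated", with a two-sided 5% level. The target is "to achieve a power of 80% to reject at least one comparison", under the condition "when at least one difference between groups has an effect size of d = 0.5". The effect size comes from a minimal important difference of 5 and a standard deviation of about 10. Drop-out is described as having no quality-of-life data after the intervention, and the sentence ends: "data available after intervention, see 7) of 20%, 90 patients per group should be recruited".

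The total agrees with 3 × 90 elsewhere. The Abstract gives 270, and Study population says "The study will recruit 270 adult cancer patients with non-curable disease".

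The same section says that a linear mixed model will be used and will deal with missing values. The Data analysis section adds that the model for the primary endpoint adjusts for recruitment setting, availability of a relative, gender, ECOG and baseline FACT-G. Neither section uses the model or the adjustment to justify a smaller allowance for drop-out.

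**The concern.** The recruitment target should follow from the required number and the assumed loss. Here it does not, and the 270 built on it is the trial's headline size. A reader who takes the section at face value will believe that the trial can lose a fifth of its patients and still have 80% power on the stated inputs. That matters most for a null result on the primary endpoint, where the printed justification is what readers use to judge whether a difference of 5 points could have been missed. The tolerance for loss is also of practical importance in this population, because the Limitations section names death before the primary endpoint as the first weakness of the design.

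**Working it through.** **Inputs from the article.** Difference 5 and SD 10, so d = 0.5; two-sided 5%; power 80% for at least one comparison; 77 per group required; 20% drop-out; 90 per group recruited; equal allocation to three arms.

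**Assumption.** The article does not give the number of comparisons or the level of each. I tried one, two and three comparisons with the 5% divided equally.

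**Step 1: reproduce 77.** Per group, n = 2(z₁₋α/₂ + z₀.₈₀)² / d².

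- One comparison, α = 0.05: n = 63.
- Two comparisons, α = 0.025: 2(2.241 + 0.842)² / 0.25 = 76.04, so n = 77.
- Three comparisons, α = 0.05/3: n = 84.

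Two comparisons at 0.025 return the stated 77. It is therefore a number before drop-out. An omnibus F-test with means 0/0.25/0.5 SD would need 79.

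**Step 2: inflate for drop-out.**

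- Correct: 77 / (1 − 0.20) = 96.25, so 97 per group and 3 × 97 = 291 in total.
- Common shortcut: 77 × 1.20 = 92.4, so 93 per group.
- Stated: 90 per group, 270 in total.

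Neither route gives 90. The plan is 7 per group (21 in total) below the correct figure. Read backwards, 90 × 0.80 = 72 evaluable, which is 5 per group short of 77. The loss that 90 can absorb is 1 − 77/90 = 14.4%.

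**Step 3: power of a single comparison at α = 0.025, unadjusted.** The mean of the test statistic is d√(n/2).

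- n = 72: 0.5 × √36 = 3.00; Φ(3.00 − 2.241) = 77.6%; noncentral t gives 76.8%.
- n = 77: 0.5 × √38.5 = 3.10; Φ(3.10 − 2.241) = 80.5%; noncentral t gives 79.8%.

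The F-test with means 0/0.25/0.5 gives 76.5% at 72 and 79.4% at 77.

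**Step 4: power on the plan's own criterion, at least one rejection.** I take two comparisons of col-ACP with the two controls. They share an arm, so their statistics correlate 0.5. Power = 1 − P(|Z₁| ≤ 2.241 and |Z₂| ≤ 2.241), by the bivariate normal distribution.

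| True differences (SD) | 72 per group | 77 per group |
|---|---|---|
| 0.5 and 0 | 78.5% | 81.4% |
| 0.5 and 0.25 (means 0/0.25/0.5) | 78.9% | 81.7% |
| 0.5 and 0.5 | 89.7% | 91.6% |

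**Step 5: effect of the planned baseline adjustment.** With correlation r between baseline and week-16 FACT-G, the residual SD is 10√(1 − r²). The article gives no r, so a range is shown. Single comparison, α = 0.025, 72 per group, noncentral t:

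| r | Power |
|---|---|
| 0 | 76.8% |
| 0.2 | 78.6% |
| 0.27 | 80.1% |
| 0.3 | 80.9% |
| 0.5 | 88.3% |

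**The case against.** Three arguments can be made for the plan.

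**The analysis is stronger than the calculation.** A reader might infer from 72 against 77 that the trial will not have 80% power. The article does not support that. Its primary model adjusts for baseline FACT-G, and Step 5 shows that a correlation of about 0.27 is enough to restore 80% at 72 per group. Since r is not given, power under the planned analysis is unknown, and it may well exceed 80%. This stands, and it limits the point to the stated figures. It does not make 77, 20% and 90 consistent, because the power section neither claims this gain nor states a correlation.

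**The mixed model handles missing data.** This helps little for the loss counted here. Patients without any quality-of-life data after the intervention contribute almost nothing to the treatment contrast at week 16.

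**The size depends on a reconstruction.** The per-test level of 0.025 is solved back from 77, and single-test power is not the plan's criterion. This is also fair. On the stated criterion the shortfall is only 1 to 2 points in the less favourable configurations, and there is none if col-ACP exceeds both controls by 0.5.

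A reader might also infer that loss at the primary endpoint must exceed 20%, because a patient with the week-10 assessment (T1) but not the week-16 assessment (T2) would count as retained. The wording allows that reading but does not settle it. The definition refers to another section that the article does not contain, so this can be raised only conditionally.

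**Conclusion.** The three figures are inconsistent as printed, and this holds without any assumption: 77 evaluable at 20% loss needs 97 per group, and 90 leaves 72. The effect on power is modest. On unadjusted inputs with two comparisons at 0.025 each, the shortfall against 80% is about 3 points for a single comparison and 1 to 2 points for at least one rejection in the minimum case that the plan states. It disappears if col-ACP exceeds both controls by 0.5, or if the baseline correlation reaches about 0.27 under the planned model. The finding is that the stated recruitment number does not follow from the stated inputs; it does not show that the trial is underpowered.

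**What to change.** Correct the paragraph in one of these ways, none of which needs more patients:

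- State that 90 per group tolerates about 14% loss while keeping 77 evaluable.
- Keep the 20% and state that it leaves 72 evaluable per group, with about 77% power for a single comparison and about 79% for at least one when only one difference is 0.5.
- Keep 80% at 90 per group, base it on the baseline-adjusted model, and state the assumed correlation between baseline and week-16 FACT-G (at least about 0.27) and its source.

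In each case, state the number of comparisons and the level of each. Check the full drop-out definition as well. If it counts patients with T1 but no T2 as retained, align it with missing FACT-G at T2, because loss at the primary endpoint would then be at least as large as the stated 20%.

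The cost is one paragraph of wording. Under the first two options the stated tolerance or power becomes slightly less favourable; the third adds an assumption that must be defended. Recruiting 97 per group would also reconcile the figures, at the price of 21 more patients.

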#### Selection and attrition bias

In order to avoid a potential selection bias all palliative cancer patients at a screening site will be screened for eligibility. If pre-screened patients meet inclusion criteria they will be approached and asked to participate in the study. We examine potential attrition bias by carefully analysing drop-outs. In accordance with the intention-to-treat principle, the data of all patients randomised to the treatment groups will be analysed. When a drop-out occurs due to the death of a patient, bereaved relatives will be followed up if approved.

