### Data analysis

For the primary endpoint, a linear mixed model will be fitted with independent variable intervention group and additional covariates recruitment setting, availability of a relative (strata from randomisation according to ICH E9), gender, ECOG and FACT-G at baseline. Analyses of the key secondary endpoint will be performed in the same way using linear mixed models. Additional analyses for the complete follow up data will be done using repeated measure models. An intention-to-treat population will be used for all analyses. Data analysis will be conducted by the department of biometry of the Ruhr-University which is not engaged in the intervention or data collection.

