### Limitations

This study has limitations that need further consideration. First, our study collective is vulnerable towards loss of patients due to death before collection of the primary endpoint. Predicting patient’s life-expectancy in palliative cancer care is difficult, we therefore collaborate with experienced clinicians reviewing pre-screened patients. Second, in previous advance care planning trials quality of life as a primary endpoint has been difficult to improve [16]. QoL is influenced by many factors such as burden of disease, pain, and distress. We chose QoL as the primary outcome of our study because it is the primary and important goal of palliative care, but in addition investigate other highly relevant outcomes. Third, we conduct a complex intervention that needs highly skilled and trained facilitators. Our study personnel conducting the intervention are trained psychologists, which can be a challenge for broader implementation of our intervention.

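### Death is treated as missing quality of life: the plan does not say what the week-16 FACT-G comparison means for patients who have died, or whether the 20% drop-out allowance includes them

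*Protocol article*

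**What the plan says.** All references are to the Protocol article.

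- **Power calculation, sample size, recruitment.** The calculation gives 77 per group, raised to 90 for an assumed 20% drop-out, defined as having no quality-of-life data after the intervention. It then states: "We have to expect about 130 to 155 events of death in our patient population", depending on the assumed one-year survival. The primary hypotheses are to be tested with a linear mixed model. The section says this model supplies estimates where values are missing and uses the full intention-to-treat sample.
- **Selection and attrition bias.** All randomised patients are to be analysed and drop-outs examined. Death is named as one cause of drop-out: "When a drop-out occurs due to the death of a patient, bereaved relatives will be followed up if approved".
- **Data analysis.** The primary model has intervention group as the independent variable and baseline FACT-G among the covariates. Separately, "Additional analyses for the complete follow up data will be done using repeated measure models". The intention-to-treat population applies to every analysis.
- **Limitations.** The article concedes that "our study collective is vulnerable towards loss of patients due to death before collection of the primary endpoint". Its answer is clinician review of pre-screened patients; nothing is said about the analysis.
- **Study population.** Patients are excluded when the physician is certain they will not live four months.

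**The concern.** Taken together, these sections make death a drop-out, drop-out a missing value, and missing values something the model estimates for everyone randomised. No section makes an exception for death.

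A living patient who does not return the questionnaire has a FACT-G score that was not seen. A patient who has died has no score. With about half the cohort expected to die within a year, the distinction decides what the primary result means. If mortality differs between arms, a comparison of those still able to answer tends to favour the arm that has lost more of its sickest patients. The same question bears on sample size, because the article does not say whether its drop-out allowance is meant to absorb deaths. From T3 to T7 the problem grows as deaths accumulate.

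**Working it through.** **1. The plan's own sample size.** Inputs from the sample-size section: difference 5, SD about 10 (d = 0.5), two-sided 5%, and 80% power "to achieve a power of 80% to reject at least one comparison". Splitting the 5% over two comparisons gives α = 0.025:

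n = 2 × (2.241 + 0.842)² × (10/5)² = 76.04, rounded up to 77 per group. The stated figure is reproduced.

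**2. What 90 per group covers.** Allowing for a 20% loss requires 77 / 0.80 = 96.25, so 97 per group. With 90, a 20% loss leaves 90 × 0.80 = 72. The loss that 90 can absorb is 1 − 77/90 = 14.4%.

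**3. One-year mortality implied by the plan.** 130/270 = 48.1% and 155/270 = 57.4%, so one-year survival S is 0.519 or 0.426.

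**4. Deaths by T1 (week 10) and T2 (week 16).** The article gives neither figure, so a hazard shape k has to be assumed: proportion dead by week w = 1 − S^((w/52)^k). k = 1 is a constant hazard. k = 1.5 and k = 2 represent a lower early risk, as the four-month exclusion might produce. For example, with k = 1: 1 − 0.519^(16/52) = 18.3% and 1 − 0.426^(16/52) = 23.1%. Each range runs from 130 to 155 deaths.

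| Assumed hazard | Dead by week 10 | Dead by week 16 | Week-16 deaths as share of 20% | As share of 14.4% | Alive at week 16, per 90 |
|---|---|---|---|---|---|
| Constant (k = 1) | 11.9–15.1% | 18.3–23.1% | 92–115% | 127–160% | 73.5–69.2 |
| k = 1.5 | 5.4–6.9% | 10.6–13.6% | 53–68% | 73–94% | 80.5–77.8 |
| k = 2 | 2.4–3.1% | 6.0–7.8% | 30–39% | 42–54% | 84.6–83.0 |

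**5. Adding living non-responders.** With 5% to 10% non-response among survivors (assumed), the evaluable number runs from 84.6 × 0.95 = 80.3 down to 69.2 × 0.90 = 62.3 per group. Two-sample t-test power at d = 0.5 and α = 0.025 is then 0.82 down to 0.70, without baseline adjustment.

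**6. What the primary contrast refers to.** There are two readings.
- *Longitudinal model (baseline, T1, T2) under missing-at-random.* Nothing is inserted for the dead, but the week-16 means are those expected had everyone gone on living and reporting.
- *Week-16 data only, with baseline as covariate.* The dead leave the model. The result compares survivors who responded, and the sample-size section's claim to use the full sample does not hold.

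The sample-size section points to the first reading. The Data analysis section, which lists repeated-measures models as additional, allows the second.

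**7. Size of a survivor-selection effect (illustration).** Assume no true effect, SD 10, and a normal liability to die correlated ρ with the week-16 score. Survivors then average above the whole arm by 10 × ρ × φ(z_p)/(1 − p), where p is the proportion dead and z_p its normal quantile. For 18% v 23% dead, φ(z_p)/(1 − p) is 0.320 and 0.394, so the arms differ by 0.74ρ, or 0.2 to 0.5 points for ρ = 0.3 to 0.7. For 15% v 25% it is 0.274 and 0.424, so 1.49ρ, or 0.4 to 1.0 points. These mortality differences and correlations are assumed, and there is no adjustment for baseline FACT-G or ECOG.

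**The case against.** The other side has several good points.

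- **A reader might infer that deaths largely use up the 20% allowance.** The documents do not establish this. The 130 to 155 deaths are tied to one-year survival, and the four-month exclusion argues against a constant hazard. Drop-out is defined as no data after the intervention, so a patient who completes T1 and then dies may not count. On that reading only deaths before T1 matter, about 2% to 15%. The definition also carries a cross-reference to material not shown.
- **A reader might infer that the primary estimate contains values for people who have died.** A likelihood model inserts none. Its extrapolation is implicit, and there is none if only week-16 data are used.
- **A reader might infer that nothing in the plan would reveal unequal mortality.** The attrition section promises an analysis of drop-outs and names death as a cause.
- **The numerical harm may be small.** The illustrated bias is at most about 1 point against a minimal important difference of 5. If SD 10 is unadjusted and baseline correlates 0.5 with week 16 (assumed), power at 62 per group is 0.83.
- **The methods for T3 to T7 are open.** Repeated-measures models do not have to project past death, and the choice of method can sit in the analysis plan.

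All of this limits the size of the point, but it does not supply the missing exception. The article states a rule for missing values, applies it to all randomised patients and names death as a cause of drop-out. On the other side of the balance, the exclusion applies only where the physician is certain, and the Limitations section accepts that prognosis is hard to judge, so some deaths before week 16 must be expected.

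**Conclusion.** The point holds as a defect in the stated rule, worth correcting. The article does not separate death from missing questionnaires, so its primary contrast is either a comparison in a hypothetical cohort without deaths or a survivor comparison that conflicts with its own full-sample claim. That conclusion rests on the text alone.

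The size is uncertain because no week-16 death figure is given. Week-16 deaths of about 6% to 23% would take roughly a third to all of the 20% allowance, depending on the assumed hazard, and less if deaths after T1 are not counted. The 14.4% that 90 per group really covers needs no such assumption and leaves less room than the plan states. Any distortion of the week-16 contrast is probably modest, but the T3 to T7 analyses are more exposed, since 48% to 57% of the cohort is expected to be dead by one year.

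**What to change.** 1. State that the primary estimate is the difference in FACT-G at week 16 among patients alive then, with the mixed model covering living non-responders only and nothing estimated after death. Make the sample-size, attrition and Data analysis sections agree on this.
2. Report deaths to week 16 by arm beside the primary result.
3. Pre-specify one supporting analysis in all randomised patients that ranks death before week 16 below every observed score.
4. Define the T3 to T7 analyses as means among patients alive at each visit, by a method that does not extrapolate past death. A generalised estimating equation with independence working correlation is one option among several.
5. Restate the expected loss at T2, say whether it includes deaths, and reconcile it with the 14.4% that 90 per group covers.

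The cost is revised wording and one extra analysis. Patients are already followed until death, but vital status at week 16 must be known for every patient, including those without a participating relative. There are two drawbacks. The survivor estimate conditions on survival, which is why the all-randomised analysis belongs beside it, and the restated loss may look less favourable than the present 20%.
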